## Abstract

**Background:**

Invasive coronary angiography (ICA) is the gold standard in the diagnosis of coronary artery disease (CAD). Being invasive, it carries rare but serious risks including myocardial infarction, stroke, major bleeding, and death. A large proportion of elective outpatients undergoing ICA have nonobstructive CAD, highlighting the suboptimal use of this test. Coronary computed tomographic angiography (CCTA) is a noninvasive option that provides similar information with less risk and is recommended as a first-line test for patients with low-to-intermediate risk of CAD. Leveraging artificial intelligence (AI) to appropriately direct patients to ICA or CCTA based on the predicted probability of disease may improve the efficiency and safety of diagnostic pathways.

**Objective:**

he CarDIA-AI (Coronary computed tomographic angiography to optimize the Diagnostic yield of Invasive Angiography for low-risk patients screened with Artificial Intelligence) study aims to evaluate whether AI-based risk assessment for obstructive CAD implemented within a centralized triage process can optimize the use of ICA in outpatients referred for nonurgent ICA.

**Methods:**

CarDIA-AI is a pragmatic, open-label, superior randomized controlled trial involving 2 Canadian cardiac centers. A total of 252 adults referred for elective outpatient ICA will be randomized 1:1 to usual care (directly proceeding to ICA) or to triage using an AI-based decision support tool. The AI-based decision support tool was developed using referral information from over 37,000 patients and uses a light gradient boosting machine model to predict the probability of obstructive CAD based on 42 clinically relevant predictors, including patient referral information, demographic characteristics, risk factors, and medical history. Participants in the intervention arm will have their ICA referral forms and medical charts reviewed, and select details entered into the decision support tool, which recommends CCTA or ICA based on the patient’s predicted probability of obstructive CAD. All patients will receive the selected imaging modality within 6 weeks of referral and will be subsequently followed for 90 days. The primary outcome is the proportion of normal or nonobstructive CAD diagnosed via ICA and will be assessed using a 2-sided *z* test to compare the patients referred for cardiac investigation with normal or nonobstructive CAD diagnosed through ICA between the intervention and control groups. Secondary outcomes include the number of angiograms avoided and the diagnostic yield of ICA.

**Results:**

Recruitment began on January 9, 2025, and is expected to conclude in mid to late 2025. As of April 14, 2025, we have enrolled 81 participants. Data analysis will begin once data collection is completed. We expect to submit the results for publication in 2026.

**Conclusions:**

CarDIA-AI will be the first randomized controlled trial using AI to optimize patient selection for CCTA versus ICA, potentially improving diagnostic efficiency, avoiding unnecessary complications of ICA, and improving health care resource usage.

**Trial Registration:**

ClinicalTrials.gov NCT06648239; https://clinicaltrials.gov/study/NCT06648239/

**International Registered Report Identifier (IRRID):**

DERR1-10.2196/71726

## Introduction

Coronary artery disease (CAD) is a leading cause of death globally [1]. While invasive coronary angiography (ICA) remains the gold standard for CAD diagnosis, many patients undergoing elective ICA are found to have a nonobstructive disease or normal coronary anatomy, with variability between cardiac centers [2,3]. Despite lower population-based rates of ICA in Ontario, Canada, over 50% of elective ICA procedures find nonsignificant CAD (CorHealth Ontario, unpublished data, 2022). A low diagnostic yield of elective ICA is not only resource-intensive [4-6] but unnecessarily subjects patients not requiring invasive intervention to major procedural complications, including vascular injury, major bleeding, stroke, myocardial infarction, and death [7]. A noninvasive test able to provide similar information with less risk and cost is ideal in a lower-risk population.

Coronary computed tomographic angiography (CCTA) has emerged as one such noninvasive alternative to anatomically evaluate the coronary arteries. CCTA is highly sensitive for the detection of >50% coronary stenosis in patients with low to moderate pretest probability of obstructive CAD [8,9], is less expensive, and carries significantly less risk [10]. Appropriately, guidelines for the evaluation of chest pain from the American College of Cardiology/American Heart Association and the European Society of Cardiology both recommend first-line CCTA in this population [11,12]. However, limited access to CCTA in Canada due to limited diagnostic infrastructures has restricted its widespread use. Conversely, a CCTA-first approach can result in double-testing, since patients with abnormal CCTA frequently proceed to confirmatory or therapeutic ICA, which is wasteful and exposes patients to unnecessary radiation. Ultimately, appropriate test selection requires accurate prediction of the pretest probability of obstructive CAD.

Artificial intelligence (AI) has been leveraged to improve the prediction of significant CAD. Traditional risk assessment tools include a more limited number of variables and may not capture the full complexity of patient risk profiles. Conversely, machine learning algorithms can incorporate a greater number of predictors, including highly correlated predictors, and can account for complex, nonlinear relationships between predictors, including at the patient level [13]. We have developed an AI model to predict the probability of obstructive CAD using 12 years of referral data from 2 regional hospitals, comprising a cohort of over 29,000 patients, which significantly outperformed existing risk scores (area under the receiver operating characteristic curve of 0.81 vs 0.62) and achieved a net reclassification improvement of 44.7% over usual care (95% CI 42.4%-47.0%) [14]. The model has been updated using more recent referral data and has undergone external validation using 2008-2023 province-wide data to confirm generalizability ([name] et al, unpublished paper, April 2025). The integration of this model into clinical practice may enable a more accurate assessment of patient risk and improve diagnostic efficiencies.

A decision support tool that incorporates such an AI model within a centralized triage pathway may facilitate patient selection for first-line CCTA (Figure 1). We have established that a centralized triage model in which low-risk patients referred for ICA are considered for CCTA first can improve the diagnostic yield of elective ICA and that such a model is acceptable to both patients and referring physicians [15]. As such, we have deployed the AI model in our local cardiac center and conducted a pilot study using a silent trial design [16] to establish feasibility within the centralized triage pathway and address implementation issues ([name] et al, unpublished paper, April 2025). With the individual components of the intervention validated and piloted, the next appropriate step is to conduct a clinical trial of the intervention to measure its impact on clinical outcomes.

**Figure 1 figure1:**
[figure not shown]
AI intervention in the context of the clinical pathway. The AI model is integrated into a centralized triage model for ICA and CCTA, where community cardiologists can refer to a single unit for an angiogram for suspected obstructive CAD, and the AI model provides a recommendation for which test is most appropriate for a given patient. Green boxes indicate the optimal test for a given patient, orange indicates suboptimal testing (patient received a “double-test” of both CCTA and ICA), and red indicates the least optimal (patient received an ICA but did not have obstructive disease). AI: artificial intelligence; CAD: coronary artery disease; CCTA: coronary computed tomographic angiography; ICA: invasive coronary angiography.

The CarDIA-AI (Coronary computed tomographic angiography to optimize the Diagnostic yield of Invasive Angiography for low-risk patients screened with Artificial Intelligence) trial will evaluate whether AI-based screening within a centralized triage pathway can optimize patient selection for CCTA versus ICA. The primary goal of this study is to reduce the proportion of unnecessary ICA procedures (showing normal or nonobstructive CAD) performed in patients referred for evaluation of CAD diagnosed in patients undergoing ICA. This trial will compare the AI intervention to usual care (ie, directly proceeding to ICA) to assess improvements beyond the current diagnostic pathway.

## Methods

### Objectives

The primary objective of the CarDIA-AI trial is to determine the effect of a centralized triage process incorporating AI-based risk assessment, compared to usual care, on the proportion of normal or nonobstructive CAD diagnosed via ICA, in adults referred for nonurgent (elective) outpatient ICA.

### Study Design

The CarDIA-AI trial is a pragmatic, open-label, multicenter, superiority trial with two parallel groups and 1:1 allocation. The study was registered at ClinicalTrials.gov (NCT06648239). This protocol was prepared in accordance with the SPIRIT-AI (Standard Protocol Items: Recommendations for Interventional Trials—Artificial Intelligence) guidelines [17] (see Multimedia Appendix 1 for checklist).

### Participants

#### Setting

Two cardiac centers located in Ontario, Canada, will participate in the CarDIA-AI trial: Hamilton Health Sciences’ General Hospital (Hamilton site) and Niagara Health System’s Marotta Family Hospital (Niagara site). These regional referral centers serve a large geographic area in southern Ontario with a population exceeding 1.8 million. ICA referral forms from the region are received at the Heart Investigation Unit located at the Hamilton site. Ordinarily, triage staff categorize the referrals according to urgency and site (Hamilton or Niagara; based on the patient’s home address). For CarDIA-AI, outpatient ICA referrals will be reviewed daily to identify eligible participants.

The AI risk-assessment tool is deployed on a virtual machine housed at Hamilton Health Sciences’ research data center. The virtual machine is allocated with 8 central processing unit cores and 16 GB of RAM. The virtual machine is accessed by the research team at the study sites using Citrix.

#### Informed Consent

Eligible patients are identified by a research assistant and reviewed by a board-certified cardiologist. The research assistant will then contact eligible patients by phone to discuss the study, review the consent form, and obtain verbal informed consent. At the time of the ICA or CCTA, research staff will also obtain written, paper-based consent from patients willing to participate (Multimedia Appendix 2).

#### Sample Size

The assumed proportion of normal or nonobstructive CAD on angiogram in the control arm is based on proportions at the two participating centers over the last decade, which have been stable at 44%. Our pilot work suggests that the proportion of normal or nonobstructive CAD diagnosed via ICA in the experimental arm is expected to be around 22%. We studied the power for various possible effect sizes (reduction in event proportions). A 1:1 sample of 200 people can detect an absolute reduction of 22% or higher in event proportion with 91.9% power, and a smaller 19% absolute reduction or higher with 81.3% power. To adjust for noncompliance of up to 5% in both arms, we increased the sample size from 200 patients by a factor of 1.23 to 246 patients [18]. Adjusting for up to 2% losses to follow-up, we require 252 patients (126 per arm).

An average of 115 eligible patients are seen at the participating centers each month. Given that recruitment is carried out by a centralized administration team (individual clinicians are not required to be involved), we do not anticipate significant recruitment barriers. Thus, we conservatively expect to recruit 100 patients per month. The recruitment will take place over 3 months to achieve our target sample size.

#### Eligibility Criteria

Patients are eligible if they (1) are 18 years of age or older; (2) are referred for nonurgent (elective) outpatient ICA; (3) have an indication for ICA that includes “Rule out CAD,” “Cardiomyopathy,” “Stable CAD,” or “Stable Angina”; and (4) are able to provide informed consent in English. Patients will be excluded if they (1) have received a prior high-quality CCTA within the last five years; (2) have atrial fibrillation or other arrhythmia precluding high-quality CCTA; (3) have known severe renal dysfunction (glomerular filtration rate of <35 mL/min/1.73 m^2^); (4) have planned (coronary or noncoronary) cardiac surgery; (5) have any prior obstructive CAD, acute coronary syndrome, percutaneous coronary intervention, or coronary artery bypass graft; or (6) have known severe coronary artery calcification (calcium score >250) or not deemed to be “mild” on report if not quantified. Referral forms indicating “Stable CAD” will be reviewed to ensure the patient does not meet exclusion criteria (eg, known prior obstructive CAD), as many referring physicians check this indication without objective evidence of known CAD.

No exclusions will be made at the level of the input data after confirming patient-level eligibility. If data on the referral form are missing or of poor quality, research staff will review any additional documentation in the patient’s chart to attempt to obtain the missing data. Otherwise, the data will be imputed.

#### Randomization

Participants will be randomly assigned (1:1 allocation) to either usual care or centralized triage using AI-based CAD risk assessment. Block randomization using randomly varying block sizes (unknown to investigators and study personnel), stratified by site with a computer-generated random sequence, will be used. Research personnel will randomize participants via an interactive web response system, ensuring allocation concealment. The interactive web response system is a 24-hour computerized randomization internet system maintained by the coordinating center at Hamilton Health Sciences’ Population Health Research Institute.

### Interventions

#### Centralized Triage

Participants randomized to the intervention arm will have their referral triaged using an AI-based decision support tool to determine the cardiac imaging test they will receive. The AI model uses participants’ medical history (as documented on their referral form) to predict the patient’s probability of significant CAD. Participants deemed high risk for obstructive CAD will receive ICA as recommended by the AI model, effectively receiving usual care. Those assessed to be low risk will receive CCTA, proceeding to confirmatory or therapeutic ICA if appropriate (Figure 2). For patients undergoing CCTA, recommendations for medical management versus referral for ICA will be made based on the CCTA results as per established clinical practice guidelines (Table S1 in Multimedia Appendix 3). Participants who withdraw consent or are admitted to the hospital with concern for acute coronary syndrome after randomization will receive usual care. As our pilot study suggests that the centralized triage process is acceptable and has high fidelity [15], no specific strategies to improve intervention adherence will be implemented.

**Figure 2 figure2:**
[figure not shown]
The flow of participants through the study. AI: artificial intelligence; CAD: coronary artery disease; CCTA: coronary computed tomographic angiography; HIU: Heart Investigation Unit; ICA: invasive coronary angiography.

Only participants in the intervention arm will receive CCTA. Furthermore, interventional cardiologists require access to CCTA results to provide the best care and determine the appropriateness of subsequent ICA. As such, blinding of patients and providers is not possible.

#### AI-Based Risk Assessment for Significant CAD

As part of the centralized triage process, participants’ allocation status will be entered into the risk assessment tool prior to generating the recommendation. For patients randomized to the intervention, the AI model outputs a predicted probability of significant CAD (not shared with clinical personnel), as well as an imaging modality recommendation (CCTA or ICA) informed by the predicted probability. Participants in the intervention arm will receive the imaging modality recommended by the tool.

The AI model uses a light gradient boosting machine algorithm to predict the probability of obstructive CAD based on 42 clinical predictors, including demographic characteristics, patient referral information, anthropometric measures, clinical symptoms, risk factors, medical history, and tobacco habits, as documented on the referral forms (Multimedia Appendix 4). Based on clinical input, we included variables related to the patient’s medical history available at the time of referral, the unique physician number for each referring physician to capture patterns in referral practices, and socioeconomic variables. We selected the light gradient boosting machine algorithm based on our previous study, in which it showed the best discrimination performance among 8 machine learning models developed [14]. An analysis of variable importance and interactions between variables can be found in our previous publication [14]. The model was trained, validated, and evaluated on data from the CorHealth Ontario Cardiac Registry, a multicenter, prospectively collected registry of referral information from patients receiving ICA in the province of Ontario, Canada. The original model derivation cohort included 29,448 patients who received their ICA in the Hamilton or Niagara regions between 2008 and 2019 [14]. We subsequently externally validated the model using an additional sample of 7785 patients who underwent ICA between 2020 and 2023. This trial will use the most recent version of the model, based on 2008-2023 data from the two trial sites. The decision thresholds are 0.556 and 0.560 for the Hamilton and Niagara sites, respectively. The thresholds were optimized to maximize the difference between the true positive rate and the false positive rate (Youden index). An exhaustive description of the development, validation, and evaluation methods and results for this model will be available in a forthcoming paper ([name] et al, unpublished paper, April 2025). The AI model is not currently publicly available.

To obtain the input data for the tool, a research assistant will manually review the ICA referral forms of eligible patients and associated documentation in their chart (Figure S1 in Multimedia Appendix 3). If there are ambiguities or inconsistencies in the referral form or chart, these data will be managed based on predetermined standard operating procedures (Multimedia Appendix 5). Missing data will be imputed. Any ambiguities or inconsistencies requiring clinical interpretation will be treated as missing and imputed.

The user interface of the AI tool consists of various input fields that correspond to the model predictors (Figure S2 in Multimedia Appendix 3). Users either manually enter a value (eg, for Age) or select a value from the field drop-down menu (eg, for Referral Month). The input fields largely reflect nominal, structured data elements on the referral forms completed by referring physicians. While clinical expertise is not required to use the tool, study personnel using the tool have discussed the contents of the form at length with members of the Heart Investigation Unit in preparation for the trial.

#### Usual Care

Participants allocated to the control arm will receive usual care, meaning they proceed directly to ICA as referred. For control group participants, the AI-based decision support tool will always recommend ICA (ie, usual care) and provide the predicted probability of significant CAD, though this probability will not be shared with the clinical team.

### Outcomes

#### Primary Outcome

The primary outcome is the proportion of normal or nonobstructive CAD diagnosed via ICA, calculated by dividing the number of patients diagnosed with normal or nonobstructive CAD through ICA by the total patients allocated to that arm. This was identified as the most policy-relevant outcome for Ontario Health.

#### Secondary Outcomes

Secondary outcomes include (1) the number of angiograms avoided, (2) deviation from management recommendations following CCTA (ie, angiograms performed when not recommended), (3) the diagnostic yield of ICA (ie, number of patients diagnosed with obstructive CAD out of all patients undergoing ICA), (4) the number of low-quality CCTAs, (5) the difference in the proportion of normal or nonobstructive CAD diagnosed through ICA between male and female patients; and (6) the difference in the proportion of normal or nonobstructive CAD diagnosed through ICA between sites. Furthermore, we will assess the budget impact of the AI intervention.

### Data Collection

#### Overview

All patients will be followed for 90 days from the date of the final diagnostic procedure to capture any relevant outcomes in this stable, elective outpatient population. For patients receiving only ICA or CCTA, this would be the date of the diagnostic procedure; for patients receiving ICA after an initial CCTA, this would be the date of the ICA. All patients will have a CCTA or ICA within 6 weeks of their index referral as per provincial guidelines. Outcomes will be identified at the time one or both procedures (if indicated) are complete. We are allowing an additional 90 days from the final diagnostic procedure to capture any unplanned crossover from CCTA to ICA (see Safety). Follow-up will be done through the provincial CorHealth Ontario Cardiac Registry, housed at the Institute for Clinical Evaluative Sciences. All ICA findings in Ontario are transmitted to the provincial registry via its secure portal. We will extract ICA findings from the registry and derive our outcomes using the standard definition for normal or nonsignificant CAD: <70% stenosis on a major coronary vessel (>2 mm) or <50% stenosis on the left main. For patients who receive CCTA, a cardiologist will manually extract CCTA results from their charts as part of follow-up, as these results are not collected by CorHealth. CCTA findings will be collected in a format and structure that aligns with the CorHealth data collection standards used for ICA findings.

For each CCTA, we will assess the quality of the resulting image. The quality will be graded on a per-patient basis using a 3-class system: low quality, denoting an image in which the coronary anatomy cannot be clearly defined, requiring ICA within 90 days for clarification; suboptimal quality, denoting an image in which the coronary anatomy was equivocal for one or more nonprognostic vessels but not requiring ICA based on CCTA findings and clinical presentation; and high quality, denoting an image in which the coronary anatomy could be clearly defined.

To track participant retention, we will keep a log of all included participants to document any who are lost to follow-up, withdraw consent, or do not otherwise receive the recommended imaging intervention. Additionally, we will document all reasons for withdrawal, as well as ask whether the patient intends to proceed with usual care (if the patient is withdrawing prior to their imaging procedure). As the necessary outcome data is generated at the time of CCTA or ICA and direct participant involvement is not required for follow-up, the participant burden will be minimized.

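### The stenosis rule for deriving the ICA outcomes joins its two limits with 'or' where 'and' is needed; programmed as printed, it would class most forms of obstructive disease as nonobstructive

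*Protocol article*

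**What the plan says.** Under Primary Outcome the article states: "The primary outcome is the proportion of normal or nonobstructive CAD diagnosed via ICA". The arithmetic for each arm is set out there as "dividing the number of patients diagnosed with normal or nonobstructive CAD through ICA by the total patients allocated to that arm". One secondary outcome, the diagnostic yield of ICA, is the "number of patients diagnosed with obstructive CAD out of all patients undergoing ICA". Two further secondary outcomes compare the primary proportion between the sexes and between the sites.

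The classification behind all of these appears once, under Data Collection, Overview: "We will extract ICA findings from the registry and derive our outcomes using the standard definition for normal or nonsignificant CAD". The definition that follows is "<70% stenosis on a major coronary vessel (>2 mm) or <50% stenosis on the left main".

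Under Sample Size, the control rate comes from "proportions at the two participating centers over the last decade, which have been stable at 44" per cent. For the other arm, "the proportion of normal or nonobstructive CAD diagnosed via ICA in the experimental arm is expected to be around 22" per cent.

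**The concern.** Obstructive disease with these limits means at least 70% stenosis in any major vessel, or at least 50% in the left main. Nonobstructive disease is the complement, so both parts must be negated and joined by 'and': below 70% in every major vessel, and below 50% in the left main. The printed rule reverses the inequalities but keeps 'or'. The article 'a' before the vessel adds a second looseness, because one unaffected vessel could be taken to satisfy the first limb.

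The rule feeds the primary outcome, diagnostic yield, and the sex and site comparisons. If it were programmed literally, a patient with a 90% lesion in a major vessel and a clean left main would be counted as an unnecessary ICA. Because the denominator is everyone allocated to the arm, the primary outcome would move towards a count of who underwent ICA at all.

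**Working it through.** **1. The plan's own figures.** Inputs from Sample Size and Statistical Analysis: 100 per arm, 44% versus 22%, two-sided alpha 0.05, z test for two proportions. The article states: "A 1:1 sample of 200 people can detect an absolute reduction of 22% or higher in event proportion with 91.9% power".

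- Pooled null variance: p̄ = 0.33, SE₀ = √(2 × 0.33 × 0.67/100) = 0.0665, SE₁ = √(0.44 × 0.56/100 + 0.22 × 0.78/100) = 0.0647. Power = Φ[(0.22 − 1.96 × 0.0665)/0.0647] = 91.7%. The unpooled version gives 92.5%.
- 44% versus 25%: 81.2% pooled and 82.2% unpooled, against 81.3% stated.
- Inflation: 200 × 1.23 = 246, where 1/(1 − 0.05 − 0.05)² = 1.23; 246/0.98 = 251.02, which rounds up to 252 in two equal arms.

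The stated figures are reproduced closely. They use 44% and 22%, which are rates under the intended definition.

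**2. Truth table of the rule.** Here 'major vessel' is the worst stenosis outside the left main.

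| Major vessel | Left main | As printed ('or') | Complement of obstructive ('and') |
|---|---|---|---|
| 30% | 20% | nonobstructive | nonobstructive |
| 90% | 20% | nonobstructive | obstructive |
| 30% | 60% | nonobstructive | obstructive |
| 90% | 60% | obstructive | obstructive |

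The two versions disagree whenever exactly one obstructive limit is met. The table applies the 70% limit to the worst vessel. If one clean vessel were enough for the first limb, fewer patients still would remain obstructive.

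**3. Illustration of size in the control arm.** Take 44% nonobstructive and 1 − 0.44 = 56% obstructive, with every control patient undergoing ICA. Let s be the share of obstructive patients who meet both limits. It is not in the document, and the range below is assumed.

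- Literal control proportion = 0.44 + 0.56 × (1 − s) = 1 − 0.56s.
- Literal control diagnostic yield = 0.56s.

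| s (assumed) | Control proportion | Control yield |
|---|---|---|
| 0% | 100% | 0% |
| 5% | 97.2% | 2.8% |
| 10% | 94.4% | 5.6% |
| 20% | 88.8% | 11.2% |

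Under the intended rule the values are 44% and 56%. The literal rule returns 44% only at s = 100%, that is, if every obstructive patient met both limits.

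**4. The between-arm difference.** Let f be the fraction of obstructive intervention patients who reach ICA, also assumed. The literal intervention proportion is 0.22 + 0.56 × f × (1 − s).

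- f = 1: 78% at s = 0 and 66.8% at s = 20%. The difference from control is still 22 points (100 − 78; 88.8 − 66.8).
- f = 0.9: 72.4% at s = 0 and 62.3% at s = 20%. The apparent reduction grows to 27.6 and 26.5 points, whereas the intended rule still gives 22.

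So the literal rule would leave a difference to detect, but obstructive patients who never reached ICA would add to the apparent benefit.

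**The case against.** The strongest reply is that nobody would be misled. The article calls this the standard definition and applies it to an existing provincial registry. The sentence can be read as a list of limits by vessel: 70% for a major vessel, 50% for the left main. A decade of data at 44% is not what the literal rule would plausibly give, and a programmer who used it would see a control rate close to 100% and stop. All of this stands, and it makes the error one of wording.

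It does not remove the point. The team itself will derive the outcomes from registry findings, so this sentence acts as the specification, and no other section shown states the limits correctly. Nor is this detail left to a statistical analysis plan: the rule is stated, and stated wrongly. A plan with the right rule would conflict with the published protocol on the primary outcome.

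A reader might infer more in three ways, and the document does not support any of them.

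- That the trial's outcomes are already misclassified, or that it no longer measures unnecessary ICA. No derivation code or result is shown, and the 44% suggests that the intended rule was used historically.
- That a definite share of obstructive patients, such as almost all, would be misclassed. That depends on s, which the document does not give.
- That CCTA findings are affected too. The primary outcome and diagnostic yield are defined on ICA alone, and no defect in CCTA handling is shown.

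**Conclusion.** The rule is wrong as written. Taken literally, it classes as nonobstructive every patient whose obstructive disease lies only outside the left main or only in it, and it cannot be squared with the 44% control rate in any realistic way. The harm is conditional on the sentence being programmed as printed. In that case, for an assumed s of 0 to 20% and ICA in all control patients, the control proportion would be 100% to 89% and control diagnostic yield 0 to 11%. These figures illustrate the scale; they do not predict the trial's results.

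The planned sample size of 252 and the stated power rest on the intended rates and do not change. What is at risk is the meaning of the primary outcome and of diagnostic yield. The correction is worth making because the sentence is the only stated rule for the primary outcome and costs almost nothing to put right.

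**What to change.** In Data Collection, Overview, state the ICA outcome rule in one of two equivalent ways:

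- normal or nonobstructive CAD: <70% stenosis in every major coronary vessel (>2 mm) AND <50% stenosis in the left main; or
- obstructive CAD: ≥70% in any major coronary vessel (>2 mm) OR ≥50% in the left main, with nonobstructive as its complement.

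The second form is harder to get wrong in code. Use the same wording in the statistical analysis plan, and check the derivation program against the four cases in the truth table before analysis. The 70% and 50% limits stay as they are.

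The cost is one sentence and a short code check. No data, sample size or procedure changes, and the article says that analysis starts only after all follow-up data are in.
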